### Outcomes and data collection

An overview of the outcomes of the ZWOT-CASE study is shown in Table 7. The primary outcome is systolic blood pressure and LDL-cholesterol. Patients fill out a questionnaire prior to the endpoint-visit including physical activity (squash questionnaire), quality of life (EQ-5D and SF-12), employment (iPCQ), patient satisfaction regarding the provided care (Patient Reported Experience Measure (PREM)), self-management (Patient Activity Measure (PAM)), and anxiety and depression (Hospital Anxiety and Depression Scale (HADS)). Besides, social status, education (UCC-1 questionnaire) [25], food habits, and CV risk perception are measured by a questionnaire.

**Table 7 Tab7:** Primary and secondary outcomes

Primary endpoints	
1. Systolic blood pressure	
2. LDL-cholesterol	
Secondary endpoints	
1. 10-years cardiovascular morbidity or mortality risk (percentage) (Risk chart Dutch guideline or SMART)	
2. Smoking status	
3. Body mass index (BMI)	
4. Lifestyle (modification) (smoking cessation, healthy food habits, physical activity, motivation for modification and awareness of received advices with respect to weight, food habits and physical activity in the past year)	
5. Awareness of CVD and cardiovascular risk factors	
6. Use of adequate medication (blood pressure lowering drugs, anticoagulants and lipid lowering drugs)	
7. Morbidity (newly developed CVD)	
8. Developed comorbidity (CVD, diabetes mellitus, COPD, heart failure, atrial fibrillation)	
9. Mortality	
10. Primary treating practitioner (GP or medical specialist)	
11. Health care consumption in the past year	
12. Self-management in the past year (patient knowledge, skills, and confidence in managing one’s health and healthcare) (Patient Activity Measure (PAM))	
13. Self-measurements of blood pressure in the past year	
14. Patient satisfaction regarding the provided care in the past year Patient Reported Experience Measure (PREM)	
15. Quality of life (EQ-5D and SF-12)	
16. Anxiety and depression (Hospital Anxiety and Depression Scale (HADS)	
17. Cost-efficiency (iPCQ)	

* HIS = general practice information system

Further, a blood sample is taken for measurement of lipids (total cholesterol, HDL-cholesterol, TC/HDL-cholesterol ratio, LDL-cholesterol, triglycerides), renal function (creatinine, MDRD), glucose and for patients with CVD hs-CRP.

The endpoint visit consists of the same components as the intake consultation in the integrated programme for CVRM as described before. Data collected during the endpoint visit will be registered in the electronic medical record.

An up-to-date 10-years cardiovascular morbidity or mortality risk will be estimated according to the algorithm of the Dutch national guideline for CVRM. This algorithm is based on the SCORE-function, adapted to the Dutch population and converted from a mortality risk to morbidity and mortality risk (based on the MORGEN-cohort and the Rotterdam Study-cohort) [26–29]. The risk chart takes into account age, sex, smoking status, systolic blood pressure and total cholesterol-HDL cholesterol ratio [23, 24]. For patients taking blood pressure or lipid lowering drugs, the actual SBP and cholesterol levels during treatment are used. For patients with CVD the SMART-function will be used to calculate the CV risk [30]. This function is based on age, sex, smoking status, systolic blood pressure, history of diabetes mellitus, ischemic heart disease, cerebrovascular disease, aortic aneurysm, peripheral arterial disease, time since first diagnosis of CVD, HDL-cholesterol, total cholesterol, renal function (eGFR), and high-sensitivity CRP.

Furthermore, baseline data and data concerning health care use in the past year and in the period prior to the study will be collected by scrutinizing the electronic medical files.

Finally, GPs will be asked to complete a survey about the CVRM care, including questions on the practice setting (rural/urban, solo/group), organization of their practice, availability of trained PNs, CVRM programme and possibilities to refer for lifestyle treatment (social map).

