**Conclusion:**

The ZWOT-CASE study will provide insight in the effects of integrated care for CVRM in general practice in patients with CVD or at high CVD risk.

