### Study procedures

Patients will be identified at the beginning of the study in order to be able to analyse factors such as mortality and comorbidity during follow-up. The study starts when patients in the intervention group visit the general practice for an intake consultation (t = 0). After the intake visit the 1 yr follow-up period commences. After 1 yr of follow-up, patients are invited for an endpoint visit. A questionnaire will be attached to the invitation letter.

Prior to the endpoint visit, all patients who agree with participation in the study will be asked to fill out the questionnaire at home. The timeline of the study procedures is represented in Fig. 1.

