#### Ethical aspects and informed consent

General practices in both groups will not be informed about which patients are identified at baseline to prevent any influence on their management. Consequently, it will not always be possible to take into account the life expectancy, cognitive function and language skills of the identified patients at baseline, as information on these exclusion criteria is not always adequately registered in the medical records. Just before the end of follow-up, GPs will be informed about the identified patients and asked to assess these exclusion criteria.

Also, at baseline patients in both groups will not yet be informed about the study to prevent that they are aware of being observed and modify their behaviour (Hawthorne effect). Based on the Dutch law for data protection, obtaining informed consent for the identification of patients is not necessary. All obtained data (age, gender and risk category) during the identification will be processed pseudo anonymised and the key to the data will be kept within the general practices. The researchers do have access to this information. Baseline data will be collected retrospectively for all patients as patients are not invited for a baseline visit in the context of the study.

Written informed consent is obtained by the GP or PN during the end-point visit and includes an agreement stating that he or she i) is sufficiently informed, had the opportunity to ask additional questions and had enough time to make a decision; ii) agrees with voluntary participation and at any time can withdraw from participation; iii) agrees with use of medical data and data of questionnaires for the purposes described in the information form; iv) agrees with the storage of the study data for 15 years after this study.

The study was reviewed by the Isala hospital Review Board and exempted from full assessment under the Medical Research Involving Human Subjects Act on the 16th of June 2016 (reference number 16.06104).

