### Statistical analyses

The aim of the main analysis is to compare the SBP and LDL-cholesterol levels after 1 yr of follow-up between patients in the intervention group receiving integrated care for CVRM and the patients in the usual care group receiving usual CVRM care. For the main analysis we will use linear regression. For secondary outcomes, linear regression will be used for continuous outcomes, logistic regression for dichotomous outcomes and multinomial logistic regression for categorical outcomes. All analyses will be corrected for clustering.

Given that patients of clusters of patients are not randomly allocated to the intervention or usual care group, we anticipate that differences in baseline risk might be present between both groups. Hence, we will adjust the analyses for these confounders, including patient characteristics and practice characteristics. To do such adjusted analysis we a priori define the following baseline covariates which are well-known to be related to the outcomes: i) patient characteristics, including relevant medication use, such as blood pressure lowering drugs [32], anticoagulants [33] and lipid lowering drugs [34], relevant comorbidity, including COPD [35], heart failure [36, 37], atrial fibrillation [38], renal failure [39], ii) practice characteristics, such as involved disciplines in CVRM care (including number of PNs) [31], number of patients, and number of GPs. Results will be reported both without (i.e. crude results) and after correction for confounders. Confounders are defined a priori and not selected based on statistical significance.

Furthermore, we will examine whether the effect of the integrated care for CVRM is modified by differences in the following practice characteristics: practice organization (solo/duo/group), availability of CVRM protocol and existence of other disease management programmes (COPD, DM). This will be done by adding interaction effects.

All analyses are applicable to patient data matched on age and gender.

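### Quality of life, anxiety and depression, and patient activation are measured only at 1 year in a non-randomised comparison, and the named covariates include no predictor specific to earlier distress or quality of life

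*Protocol article*

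**What the plan says.** **Timing of the scales.** Under Outcomes and data collection: "Patients fill out a questionnaire prior to the endpoint-visit including physical activity (squash questionnaire), quality of life (EQ-5D and SF-12"). The same sentence lists PAM for self-management and "anxiety and depression (Hospital Anxiety and Depression Scale (HADS")). In Table 7 these are secondary endpoints 12 (PAM), 15 (EQ-5D and SF-12) and 16 (HADS). Study procedures places the questionnaire at the end of follow-up. Of the invitation to the endpoint visit it says "A questionnaire will be attached to the invitation letter", and then "Prior to the endpoint visit, all patients who agree with participation in the study will be asked to fill out the questionnaire at home".

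**Baseline.** Ethical aspects and informed consent states: "Also, at baseline patients in both groups will not yet be informed about the study". The reason given is to avoid a Hawthorne effect. It adds: "Baseline data will be collected retrospectively for all patients as patients are not invited for a baseline visit in the context of the study". Outcomes and data collection names the electronic medical files as the source.

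**Allocation.** Setting says that practices chose whether to join the programme. Recruitment reports that 26 of 56 practices joined the study, 17 with the programme and 9 with usual care. Matching is on age, gender and risk group.

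**Analysis.** Statistical analyses says: "For secondary outcomes, linear regression will be used for continuous outcomes", with other regression types for other outcome scales and correction for clustering throughout. One set of confounders, defined in advance, is named for the analyses:
- blood pressure lowering drugs, anticoagulants and lipid lowering drugs;
- COPD, heart failure, atrial fibrillation and renal failure;
- disciplines involved (including practice nurses), number of patients and number of GPs.

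**Limitations** concedes the lack of random allocation. It answers that complete records, matching and multivariable analysis are ample protection against confounding.

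**The concern.** When arms are not randomised, the most useful adjustment variable for a patient-reported score is usually that score at baseline. Here it cannot exist: patients did not know of the study at t = 0 and received no questionnaire then. The covariates that are named suit blood pressure and LDL-cholesterol. They carry only indirect information on how distressed, well or activated a patient was before the programme began.

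The arms may also differ at patient level. Under Sample size calculation the expected response is 70% with the programme and 50% under usual care, because usual-care patients may be less accustomed to visiting the practice. That reason plausibly relates to activation, which PAM measures.

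At stake is how three secondary endpoints are read. A difference that existed before t = 0 would look the same at 1 year as one produced by the programme, and the named adjustment set is poorly placed to tell them apart.

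**Working it through.** **Step 1: can a baseline value exist?** The questionnaire goes out with the endpoint invitation, patients are not informed at baseline, and there is no study baseline visit. The intake consultation (Table 5) covers smoking, diet, alcohol, physical activity and stress, but none of these four instruments. Usual-care patients have no intake at all. Nothing in the article says that the medical files hold such scores. Figure 1 is not shown, but the text leaves no room for a baseline questionnaire.

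**Step 2: does the adjustment supply a substitute?** Matching factors and named covariates are listed above. None is a prior diagnosis of anxiety or depression, a psychotropic prescription, or a measure of quality of life or activation. Education and social status are collected in the questionnaire but are not named as covariates.

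**Step 3: the plan's own figure.** The 370 per arm concerns SBP and LDL-cholesterol only, and no SD is stated, so it can only be solved backwards. Inputs from Sample size calculation are 17 and 9 practices, ICC 0.05, alpha 0.05 (taken as two-sided) and power 80%.
- Cluster sizes: 370/17 = 21.8 and 370/9 = 41.1.
- Design effects, DE = 1 + (m − 1) × 0.05: 2.04 and 3.01.
- SE of the arm difference in SD units: √((2.04 + 3.01)/370) = 0.117.
- Detectable difference: (1.96 + 0.84) × 0.117 = 0.327 SD. This implies SDs of 5/0.327 = 15.3 mmHg and 0.3/0.327 = 0.92 mmol/L.

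These are plausible, but they say nothing about endpoints 12, 15 and 16, for which no effect size is given.

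**Step 4: illustration of what an imbalance would do.** Assumptions, none of them in the documents: a pre-existing difference d0 = 0.2 SD not absorbed by matching or the named covariates; a correlation ρ of 0.5 to 0.7 between baseline and 1 year; 370 per arm analysed; and an ICC for these scales of 0.02, or 0.05 borrowed from the SBP/LDL calculation.
- Remaining difference at 1 year under no programme effect: b = ρ × d0 = 0.10 to 0.14 SD.
- SE at ICC 0.02: DEs are 1.42 and 1.80, and √((1.42 + 1.80)/370) = 0.093.
- Probability of a nominally significant result: Φ(b/SE − 1.96) + Φ(−b/SE − 1.96).

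| ICC | SE (SD units) | b = 0.10 | b = 0.14 |
|---|---|---|---|
| 0.05 | 0.117 | 14% | 22% |
| 0.02 | 0.093 | 19% | 32% |

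With d0 from 0.1 to 0.3 SD and ρ from 0.5 to 0.8, b runs from 0.05 to 0.24 SD. At ICC 0.05 the probability then runs from 7% to 54%. With d0 = 0 it is 5%.

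**The case against.** Several points on the other side are fair.

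- **The design is declared and its main weakness disclosed.** The article calls the study observational, promises crude and adjusted results, and says under Limitations that lack of randomisation may bias estimates in either direction. Leaving patients uncontacted at baseline is a deliberate choice with a stated reason. All of this stands, and the point does not ask for it to be reversed.
- **The covariate list is open.** It is introduced with *including* and *such as*, and a fuller document could add outcome-specific covariates. That stands in part. But the article says confounders are defined in advance, and what it names does not fit these outcomes.
- **Adjustment is more than the drug and comorbidity lists.** Matching, practice nurse involvement and prior health care use (also to be collected) may absorb part of a difference. This also stands.
- **The imbalance is hypothetical.** The 0.2 SD, the correlations and the ICC for these scales are assumed. The calculation shows sensitivity, not that bias is present.
- **The proxies are imperfect.** Recorded diagnoses and prescriptions say little about activation, and coding may be incomplete; the article itself warns that some exclusion criteria are not always adequately recorded.

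A reader might infer that the plan promises a change analysis for these scales, or that no conclusion about effect may ever be drawn from them. The documents support neither. For secondary outcomes only regression types are named. The abstract's sentence that the study "will provide insight in the effects of integrated care for CVRM in general practice" is general and mentions none of these endpoints. Whether an observational study may speak of effects is a matter of judgement.

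**Conclusion.** The point holds in a limited form. For endpoints 12, 15 and 16 no baseline-adjusted or change analysis is possible, and neither matching nor the named covariates include a predictor specific to prior distress or quality of life. The reassurance under Limitations rests on prior record data, matching and multivariable analysis. It does not hold for these scales, because no prior score exists and no proxy is named.

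The size and direction of any bias are unknown. The 14–32% range depends wholly on the assumed 0.2 SD pre-existing difference, the correlations of 0.5 to 0.7 and the two ICC values. It should not be quoted as the error rate of this study. The primary outcomes are not touched by this point.

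**What to change.** 1. In Statistical analyses, for endpoints 15 and 16, add covariates recorded before t = 0 in the medical files of both arms: an anxiety or depression diagnosis, and a psychotropic prescription in the preceding year.
2. For endpoints 12, 15 and 16, add education and social status, which the questionnaire already collects. Both are reported at 1 year, so the write-up should say that they are taken as stable over the follow-up.
3. Describe these three endpoints as adjusted between-group differences at 1 year.
4. Under Limitations, state that they have no baseline value and that no record-based proxy exists for PAM.

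The cost is two more fields in an extraction that is already planned, some wording, and a more cautious claim for three secondary endpoints. Coding of diagnoses may be incomplete, possibly to a different degree in the two arms, so residual confounding would remain and should be acknowledged.

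### The 10-year risk endpoint takes its percentage from two functions, and the analysis rule as written would model them together with no risk-group term (minor)

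*Protocol article*

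**What the plan says.** All references are to the protocol article.

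- **Endpoint.** Table 7 (Outcomes and data collection) lists first among the secondary endpoints "10-years cardiovascular morbidity or mortality risk (percentage) (Risk chart Dutch guideline or SMART". It is one row and one percentage.
- **Functions.** The text below the table starts from the Dutch guideline: "An up-to-date 10-years cardiovascular morbidity or mortality risk will be estimated according to the algorithm of the Dutch national guideline for CVRM". It then adds: "For patients with CVD the SMART-function will be used to calculate the CV risk". The section on the programme for individual patients also ties the chart to patients without CVD.
- **Inputs.** For the chart: "The risk chart takes into account age, sex, smoking status, systolic blood pressure and total cholesterol-HDL cholesterol ratio". SMART also uses diabetes and vascular history, and its list ends with "time since first diagnosis of CVD, HDL-cholesterol, total cholesterol, renal function (eGFR), and high-sensitivity CRP".
- **Model.** Statistical analyses states: "For secondary outcomes, linear regression will be used for continuous outcomes, logistic regression for dichotomous outcomes". The a priori covariates are medication, comorbidity and practice characteristics. The effect modifiers are practice characteristics only. Risk group is in neither list, and the closing sentence names only age and gender as matching variables.
- **Design.** The study population section plans 185 CVD and 185 high-risk patients in each arm. The Matching section names age, gender and risk group, set at the beginning of the study. Under Usual care group (Recruitment), after two refusals a replacement is drawn at random from the remaining usual care patients; the text does not say that it must come from the same risk group.

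**The concern.** The two functions are different instruments with different inputs, applied to different populations. The Statistical analyses section fixes a model type, a covariate list and a list of interactions. Applied to this endpoint as they stand, they give one regression on a mixture of chart and SMART values with nothing to separate the two.

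Three things are at stake:

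- **Interpretation.** A pooled coefficient averages a chart difference and a SMART difference, and may describe neither group.
- **Precision.** The gap between the two functions enters the residual variance unless risk group, or something closely related to it, is in the model.
- **Protection against imbalance.** If the arms end with unequal shares of CVD patients, part of the gap appears as an apparent treatment difference.

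The study aim is a more favourable CV risk profile, and this is the first-listed secondary endpoint, so the analysis should be unambiguous.

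**Working it through.** The article gives no effect size, SD or power for this endpoint; the sample size section covers SBP and LDL-cholesterol only. There is no stated figure to reproduce beyond the group counts: 185 + 185 = 370 per arm and 2 × 370 = 740, which agree with the text.

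Let D be the mean gap in percentage points between SMART values in CVD patients and chart values in high-risk patients, and SD the spread within one function. The documents give neither. D = 5 to 20 and SD = 7 to 10 are assumptions. Clustering is ignored throughout.

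**1. Bias under the planned balance.** Artefact in the unadjusted pooled difference = D × (CVD share in intervention − CVD share in usual care) = D × (185 − 185)/370 = 0 for any D. The pooled difference is then the equal-weight mean of the two within-group differences. For example, within-group differences of −1 and −4 give (185 × (−1) + 185 × (−4))/370 = −2.5.

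**2. Added variance.** For a 50:50 mixture, pooled SD / within SD = √(SD² + D²/4)/SD.

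| D | SD | Ratio |
|---|---|---|
| 5 | 10 | √106.25/10 = 1.03 |
| 10 | 7 | √74/7 = 1.23 |
| 15 | 7 | √105.25/7 = 1.47 |

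In the middle case the variance ratio is 74/49 = 1.51, so 740 patients give the precision of about 740/1.51 = 490. The planned medication covariates may absorb part of this.

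**3. Loss of balance.** Suppose usual care ends with 175 or 165 CVD patients of 370 and the intervention arm has 185.

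| D | 10 short: D × 10/370 | 20 short: D × 20/370 |
|---|---|---|
| 5 | 0.14 | 0.27 |
| 10 | 0.27 | 0.54 |
| 20 | 0.54 | 1.08 |

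How could such a shortfall arise? The sample size section expects a 50% response in usual care. If refusals are independent, two refusals occur in 0.5 × 0.5 = 25% of matched sets, or 0.25 × 370 = 92.5 sets, of which 46.25 are CVD sets. If all these places were filled from a pool with CVD share p, the shortfall would be 46.25 − 92.5p. It is 10 when p = 36.25/92.5 = 0.39, and 20 when p = 26.25/92.5 = 0.28. The article does not give p, and enforcing the target of 185 per group would prevent the shortfall.

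**4. Splitting, pooling or adjusting.** Relative to a comparison of 370 per arm at the within-function SD, the standard error is multiplied by:

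- √2 = 1.41 for each separate analysis of 185 per arm;
- the ratio in step 2 for the pooled model without a risk-group term (1.23 at D = 10, SD = 7);
- about 1.00 for a combined model with a risk-group term, if the two SDs are equal.

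Pooling without the term is worse than splitting only when D > 2 × SD. Within the range in step 2, that occurs only near the corner D = 15, SD = 7 (15 > 14).

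**5. Change of function during follow-up.** At an assumed 1 to 3% new CVD per year, 1.85 to 5.55 of 185 high-risk patients per arm would gain a CVD diagnosis. A difference of 1 to 4 such patients between arms moves the pooled difference by D × k/370: from 5 × 1/370 = 0.01 to 20 × 4/370 = 0.22 points.

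**The case against.** The strongest reply is that pooling is nowhere stated for this endpoint. The article gives a general rule, the design is built on risk group throughout, and the Strengths section foresees subgroup analysis. A condensed article may leave the within-group split to the full plan. This stands in part: the mixture follows from applying the general rule, not from an explicit statement. But the section does commit to covariates and interactions, and risk group, a matching variable, is missing from them and from the closing sentence on matching.

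A reader might go further in three ways that the documents do not support:

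- **That the pooled figure is not a risk difference at all, or is biased by the mixture.** Both outputs are presented as a 10-year risk in percent. With equal shares per arm the gap cancels (step 1), leaving an average of two within-group differences.
- **That patients with new CVD switch from chart to SMART, and do so differently by arm.** An up-to-date risk and SMART for patients with CVD allow this reading. However, that label is also the name of the enrolled group, and no rule is given. The Usual care section says that systematic invitation and regular follow-up are not routine; it does not say that complaints go unasked before the endpoint visit. Step 5 shows that the effect would be small in any case.
- **That splitting is needed for precision.** It usually costs precision (step 4). The case for within-group results is interpretation.

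It is also fair to object that keeping the chart value in a patient who has since developed CVD departs from the chart's stated scope. That is accepted as a convention for the analysis only.

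**Conclusion.** The point holds in a limited form. One endpoint row draws on two functions, and the general analysis rule, followed as written, combines them without a risk-group term. Under the planned 185/185 split this does not bias the comparison. It yields an average of differences from two models, with an SD inflated by 3 to 47% for an assumed gap of 5 to 15 points and SD of 7 to 10, before any absorption by other covariates. If random replacement left usual care 10 to 20 CVD patients short, the artefact would be about 0.1 to 1.1 points for an assumed gap of 5 to 20. Change of function adds at most about 0.2 points under the assumptions in step 5. The gap, the SD, the shortfall and the rate of new CVD are all assumptions. The point is minor: it concerns one of 17 secondary endpoints and touches neither primary outcome.

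**What to change.** In Statistical analyses, add for this endpoint:

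1. Compare the arms within risk group at t = 0: chart risk in patients enrolled as high risk, and SMART risk in patients enrolled with CVD.
2. If a combined estimate is also reported, include risk group as a term and describe the result as an average over two functions.
3. For this analysis, fix the function by risk group at t = 0, and count CVD that develops during the year under secondary endpoint 7. This does not affect how risk is estimated in care.

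The cost is wording only. Risk group is already recorded for matching, and the chart's five inputs are collected for everyone at the endpoint visit. The downside is that each within-group estimate rests on about 185 patients per arm, so it is less precise than a combined estimate adjusted for risk group (standard error about 1.41 times as large, ignoring clustering and assuming equal SDs).
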